### Data analysis

Because of the exploratory nature of the analysis, we did not conduct an exact sample size calculation. However, some power assessments were performed. For our purposes, we only consider microcephaly, because the variability with regard to the frequency of microcephaly is considerably smaller than that of other congenital abnormalities currently included in the CZS definition. Based on estimates of the Latin American Collaborative Study on Congenital Malformations (ECLAMC) [77], we assume a baseline risk of 0.025% for microcephaly in children born to ZIKV-uninfected mothers. For mothers ZIKV-infected during pregnancy, we assume a probability of microcephaly between 0.25 and 6% (relative risks between 10 and 240) [19, 20, 37, 78–81]. Furthermore, we assume that the probability of a ZIKV infection during pregnancy ranges between 5 and 30%. With a sample size between 5000 and 6000 we can detect, with 80% power and significance level α = 0.05, a relative risk of 20 when the probability of ZIKV infection is 10% or higher, and a relative risk of 30 when this probability is 5% or higher.

#### PW study

Data analysis will be carried out according to a pre-specified statistical analysis plan. The characteristics of the PW included will be assessed in a descriptive analysis, taking into account the grouping of the PW by ZIKV infection status. Possible differences between the infection groups will be detected by appropriate measures of location and corresponding tests (e.g. t-test, chi-square test, Wilcoxon rank-sum test). The primary endpoint will be any congenital abnormality or adverse pregnancy outcome, based on the emerging definition of the CZS [32]. Any congenital abnormality will be assessed at birth but may be updated if an abnormality only becomes apparent later in the neonatal period. In a first step, the primary endpoint will be analysed by a chi-square test. Next, a generalised mixed model will be fitted which contains predefined basic variables. The model will be investigated and modified by a stepwise back- and forward variable selection of the fixed effects. The region (represented by the local partner site or by a group of sites) will be included as a random effect in the model and will account for the heterogeneity between different regions. Sites may be aggregated based on geographical proximity in case of data sparseness. Interaction effects between two variables will only be included if there is a clinical rationale. We will present odds ratios as results of the generalised mixed model. Throughout the analyses, we will use α = 0.05 as significance level.

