### Pregnant women (PW) cohort study

Strong evidence has been produced for a causal relationship between ZIKV infection during pregnancy and microcephaly of the baby (as well as a range of other congenital anomalies) through clinical-epidemiologic studies [8, 19–21], histopathological and virologic demonstration of ZIKV in affected tissues [22–24], and supportive evidence from in vitro studies and animal infection models [25–28]. However, the quantification of this relationship has proven difficult to measure. Co-factors or effect modifiers have been suggested to be of importance [29–31], but their exact role has not been adequately measured.

We aim to estimate the absolute and relative risk of ZIKV-associated congenital abnormalities and evaluate the role of co-factors or effect modifiers responsible for the variability of the risk currently observed across Latin America and the Caribbean, including previous exposure to other arboviruses. This will require strong support from the laboratories linked to the enrolling sites, in order to develop the expertise and tools needed to diagnose and monitor maternal, foetal and neonatal infections with high sensitivity and specificity.

**Box 1** Key Information of the ZIKAlliance Pregnant Women (PW) cohort study

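### Stepwise selection in the PW primary model puts the adjustment set, and on the stated wording the ZIKV term itself, at the mercy of the data, although the aim is to estimate the ZIKV effect

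*Protocol article*

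**What the plan says.** In the PW study subsection under Data analysis, the primary endpoint (any congenital abnormality or adverse pregnancy outcome) is first tested by chi-square. A generalised mixed model with predefined variables follows, and then: "The model will be investigated and modified by a stepwise back- and forward variable selection of the fixed effects". No entry or removal rule is given beyond the general statement "Throughout the analyses, we will use α = 0.05 as significance level". Nothing exempts ZIKV infection or the predefined variables from removal. Results are reported as odds ratios.

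Region, meaning a site or a group of sites, "will be included as a random effect in the model and will account for the heterogeneity between different regions". Whether this is a random intercept or also a random slope for ZIKV is not stated. Interactions are allowed where there is a clinical rationale, and sparse sites may be merged.

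Box 1 makes estimation of absolute and relative risks associated with ZIKV the first primary objective. The opening of the PW cohort section adds the aim to "evaluate the role of co-factors or effect modifiers responsible for the variability of the risk currently observed across Latin America and the Caribbean". The CH study subsection also fits predefined variables but describes no stepwise step. A prespecified SAP is mentioned in the PW study subsection; it is not at hand.

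**The concern.** The objective is to estimate the effect of one exposure. In that setting the adjustment set should follow from what is known about confounding, not from p-values in the same data. Stepwise selection removes real confounders whose outcome association happens to miss the cut. It then reports an odds ratio and interval as though the final model had been chosen in advance. As worded, it also undoes the protection that the predefined list was meant to give, and the exposure term is itself open to removal.

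The Discussion expects these estimates to inform resource allocation and to serve as a historical baseline for later intervention trials. Bias in the ZIKV odds ratio would carry into both.

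The secondary concern is about region. The variation the study wants to explain is variation in the ZIKV-associated risk. A random intercept absorbs differences in baseline risk only.

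**Working it through.** **1. The plan's own figures.** The Data analysis section says: "With a sample size between 5000 and 6000 we can detect, with 80% power and significance level α = 0.05", a relative risk of 20 at infection probability 10% or higher, and "a relative risk of 30 when this probability is 5% or higher". Inputs: "we assume a baseline risk of 0.025% for microcephaly in children born to ZIKV-uninfected mothers"; two-sided α assumed, since sidedness is not given. With r = uninfected/infected, the pooled-variance formula is

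n₁ = [1.96·√((1+1/r)·p̄(1−p̄)) + 0.8416·√(p₁(1−p₁) + p₀(1−p₀)/r)]² / (p₁−p₀)².

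- RR 20, 10% infected: p₁ = 0.005, p₀ = 0.00025, r = 9, p̄ = 0.1×0.005 + 0.9×0.00025 = 0.000725. Total N = 5876.
- RR 30, 5% infected: p₁ = 0.0075, r = 19. Total N = 5704.

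The stated range therefore reproduces in its upper part. Expected microcephaly cases at N = 6000 are 600×0.005 + 5400×0.00025 = 3.0 + 1.35 = 4.35, and 300×0.0075 + 5700×0.00025 = 2.25 + 1.43 = 3.68. About four cases cannot support a selected model or a regional slope, so what follows concerns the composite endpoint.

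**2. Stepwise selection with ZIKV kept in.** From the document: infection prevalence 10%, inside its planning range ("we assume that the probability of a ZIKV infection during pregnancy ranges between 5 and 30" per cent), and α = 0.05. Assumed: N = 5500, eight standardised covariates, true OR 2, baseline composite risk 3% or 10%, backward removal at p<0.05, 500 replicates. The forward step was not simulated. Columns a and b are each covariate's log OR for infection and for the outcome.

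| Risk | a | b | Coverage, full model | Coverage, selected | SE / true SD, selected | Bias in log OR, selected |
|---|---|---|---|---|---|---|
| 3% | 0 | 0.15 | 95.4% | 95.4% | 0.196 / 0.190 | −0.001 |
| 3% | 0.3 | 0.10 | 95.0% | 88.8% | 0.174 / 0.181 | +0.107 |
| 3% | 0.3 | 0.15 | 96.0% | 86.8% | 0.168 / 0.176 | +0.103 |
| 10% | 0 | 0.15 | 95.8% | 95.6% | 0.120 / 0.122 | 0.000 |
| 10% | 0.3 | 0.10 | 94.8% | 90.2% | 0.108 / 0.117 | +0.049 |
| 10% | 0.3 | 0.15 | 94.8% | 94.0% | 0.107 / 0.109 | +0.015 |

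The Monte Carlo error is √(0.95×0.05/500) ≈ 1 percentage point, so the last row is not distinguishable from the full model. Where the covariates confound, the SE is 2% (0.107/0.109 = 0.98) to 8% (0.108/0.117 = 0.92) too small. The bias multiplies the OR by e^0.015 = 1.02 to e^0.107 = 1.11. The loss is therefore mainly residual confounding, not interval width. A separate set of runs (N = 5000, 10% infected, 10% risk, 15–20 weak confounders) gave 88–93% after selection and 95–97% for the full model.

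**3. ZIKV not protected.** Same set-up with true OR 1.5, 3% risk, a = 0.3, b = 0.10: ZIKV is dropped in 28% of runs. When kept, coverage is 83% and the log OR bias is +0.214, so the typical retained OR is 1.5 × e^0.214 = 1.86. Part of that is the residual confounding seen in step 2.

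**4. Region.** Data were generated with a ZIKV log OR that varies between sites with SD τ (average OR 3, N = 5500, 10% infected). The fitted model had site-specific intercepts and one common ZIKV effect, standing in for a random intercept. Coverage for the average effect:

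| Sites, risk | τ=0 | τ=0.3 | τ=0.5 | τ=0.8 |
|---|---|---|---|---|
| 8, 3% | 95.4% | 90.5% | 78.1% | 56.5% |
| 8, 10% | 93.7% | 84.0% | 69.2% | 49.5% |
| 15, 3% | 95.2% | 91.5% | 83.9% | 60.7% |
| 15, 10% | 95.3% | 86.9% | 77.9% | 58.7% |

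At 8 sites, 3% risk and τ = 0.5, the model SE is 0.171 against a true SD of 0.252, a ratio of 1.47. The document supplies neither τ nor the number of regions in the model.

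**The case against.** **On selection.** The model does start from predefined variables, ZIKV is the subject of the first primary objective, and an unseen SAP may say that it is retained. Removal of ZIKV is therefore a possibility left open, not something the article plans. That stands. It does not rescue the stepwise step, which is stated outright: an SAP could add detail, but to remove it the SAP would have to contradict the article. The selection threshold, the confounder strengths and the event risks above are assumed, and coverage is nominal when the covariates do not confound. That also stands. The exploratory label in the Data analysis section explains why no exact sample size was calculated; it is not offered as a reason for choosing confounders by p-value.

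**On region.** A reader might infer that the plan fits region as an intercept only, that the pooled interval is therefore too narrow, and that the model cannot explain regional variation. The document does not go that far. It says a random effect without naming its form, and the covariance structure is something an SAP commonly fixes. Interactions with a clinical rationale are allowed, and the named co-factors, such as prior flavivirus infection or vaccination, could enter that way. A reader might also take the planning range of relative risks from 10 to 240 as the regional spread. It is a range of assumed microcephaly risks drawn from several cited sources, not a between-region distribution and not the composite endpoint. Sites were also chosen purposively, so whether an average over a wider set of regions is the target is itself a choice of estimand.

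**Conclusion.** The point on stepwise selection holds. The article states a method that suits exploratory risk-factor work and applies it to the model meant to estimate the ZIKV effect, with no stated protection for ZIKV or the confounders. Under assumed weak confounding, coverage falls to about 87–94% against 95–96% for the full prespecified model, mainly through bias of +0.02 to +0.11 in the log OR. If ZIKV is also open to removal, loss of the term and inflation when retained become possible; the 28% figure belongs to one assumed scenario. All sizes depend on those assumptions; the direction does not, once the covariates confound.

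The point on region is secondary and conditional. If the random effect is an intercept only and the ZIKV effect varies, the interval for the average effect can be too narrow, by an amount set by an unknown between-region SD. With no variation, coverage is nominal. It would be wrong to state narrowness as a fact of the plan.

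**What to change.** For the primary ZIKV-effect model, remove the stepwise step. Fit one confounder set, fixed on causal grounds before outcomes are examined. Leave out variables on the pathway after infection, such as symptoms of the infection itself. State that ZIKV infection status is always retained. Confine variable selection to a separate risk-factor model labelled exploratory.

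State whether the region effect is an intercept or includes a ZIKV slope. As a supporting analysis on the composite endpoint, add a random ZIKV slope by region, or a two-stage region-specific analysis with regions merged where data are sparse. Report the between-region SD and how far the named co-factors reduce it. This should not be attempted for microcephaly alone, with about four cases expected in the two power scenarios.

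The cost is wording plus slightly wider intervals. In the four confounded scenarios of step 2 the full-model SE exceeds the selected-model SE by 1% (0.108/0.107 = 1.01) to 5% (0.182/0.174 = 1.05). The regional analysis costs some geographic resolution where sites have to be merged.

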**Table Taba:** 

**Pregnant Women (PW) cohort (****clinicaltrials.gov** **identifier: NCT03188731)** **Primary Objectives** 1. To estimate the absolute and relative risks of congenital abnormalities and adverse pregnancy outcomes associated with Zika virus (ZIKV) infection during pregnancy 2. To describe the spectrum of abnormalities and adverse pregnancy outcomes associated with ZIKV infection during pregnancy, further characterizing the congenital Zika syndrome (CZS) **Secondary Objectives** 1. To improve the diagnosis of ZIKV infection in PW and neonates 2. To measure the incidence and risk factors of ZIKV infection in PW across a number of sites in Latin America and the Caribbean 3. To describe the clinical spectrum of ZIKV infection during pregnancy, and determine the proportion of symptomatic and asymptomatic infections 4. To determine the rate and risk factors of mother-to-child transmission of ZIKV (cross-cutting objective with the children [CH] cohort [see below]) 5. To evaluate the role of co-factors or effect modifiers affecting the variability of current risk estimates for congenital abnormalities 6. To compare the risk of infant abnormalities and other adverse outcomes between symptomatic and asymptomatic PW 7. To measure the association between time of ZIKV infection during pregnancy and resulting abnormalities in the foetus or other pregnancy outcomes **Inclusion/exclusion** Inclusion criteria • Age ≥ 16 years old • Confirmed pregnancy • Gestational age ≤ 27 weeks (extended to ≤32 weeks for inclusion in the first month of transmission at a location with marked transmission) • Available and willing to undergo study visits and procedures • Written informed consent (assent form and consent by a legal guardian if applicable) Exclusion criteria • Participation in another PW cohort study concerning ZIKV **Endpoints** • Congenital abnormality or adverse pregnancy outcome (according to the evolving definition of the CZS)	

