**Table Tabb:** 

**Children cohort (CH;** **clinicaltrials.gov** **identifier: NCT03393286)** **Primary Objectives** 1. To estimate the absolute and relative risks of developmental, neurological, ophthalmic, and auditory abnormalities during the first 2 years of life in children born to women infected with Zika virus (ZIKV) during pregnancy compared to women not infected during pregnancy 2. To describe the spectrum of abnormalities and clinical course during the first 2 years of life in children born to women with ZIKV, dengue virus (DENV) Chikungunya (CHIKV) or possibly other arbovirus infections during pregnancy **Secondary Objectives** 1. To evaluate risk factors for developmental abnormalities in children exposed to ZIKV during pregnancy 2. To describe the incidence of ZIKV infections after birth in early childhood and evaluate the associated risks for abnormal child development; 3. To determine the incidence of ZIKV infection in the mother after birth and evaluate its clinical features as well as its kinetics in different body fluids 4. To determine the rate and risk factors and effect modifiers for congenital, perinatal and postnatal mother-to-child transmission of ZIKV 5. To describe the kinetics and evolution of infection and immune responses to ZIKV infection in infants and children, stratified by transmission pattern (for example in utero vs. post-natal) **Inclusion/exclusion** (Fig. 3) Inclusion criteria • Group A: Infants born to mothers with confirmed ZIKV infection during pregnancy • Group B: Infants born to mothers with confirmed DENV, CHIKV or other arboviral infection during pregnancy (detected in incident fever/rash episodes) • Group C: Random sample of infants born to mothers without ZIKV/DENV/CHIKV or another arboviral infection during pregnancy (from ZIKAlliance PW cohort), 1:1 proportion compared to groups A and B together. The remaining children from mothers who were not infected with any of the three arboviruses are followed in Group D (standard visitation schedule) • Mother-infant pairs available to undergo study visits and procedures • Written informed consent (assent form and consent by a legal guardian if applicable) Exclusion criteria • Mother aged below 16 years old **Endpoints** • Infant developmental abnormalities as assessed by neurological examination, Ages & Stages Questionnaire® and Bayley Scales of Infant Development	

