#### CH study

The primary endpoint in the CH study will be the detection of any developmental abnormality within 2 years of birth. The children in the study are born to women from the PW study or to mothers with proven ZIKV infection during pregnancy. The two-year follow-up brings up the practical restriction of drop-outs as right censoring. Consequently, the primary endpoint will be analysed with survival analysis techniques. Predefined basic variables on the outcome will be included in a Cox model with region as a random factor. Specific developmental abnormalities, which are only measured at one follow-up visit, will be evaluated by mixed logistic models, containing the respective variables, with region as a random effect as above.

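### The pregnant women cohort aims at absolute and relative risks, but the result named for its model is an odds ratio; the children cohort names no risk estimate

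*Protocol article*

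**What the plan says.** **PW cohort.** Box 1, first primary objective: "To estimate the absolute and relative risks of congenital abnormalities and adverse pregnancy outcomes associated with Zika virus (ZIKV) infection during pregnancy". In Data analysis, PW study, the endpoint is a composite: "The primary endpoint will be any congenital abnormality or adverse pregnancy outcome, based on the emerging definition of the CZS". Two analyses of it are named. The first is a test: "In a first step, the primary endpoint will be analysed by a chi-square test". The second is a generalised mixed model with region as a random effect, for which the section states: "We will present odds ratios as results of the generalised mixed model". The section names no risk, risk difference or risk ratio as an output.

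**CH cohort.** Box 2, first primary objective: "To estimate the absolute and relative risks of developmental, neurological, ophthalmic, and auditory abnormalities during the first 2 years of life". In Data analysis, CH study, the method is first given in general terms: "Consequently, the primary endpoint will be analysed with survival analysis techniques". Then a model is named: "Predefined basic variables on the outcome will be included in a Cox model with region as a random factor". Abnormalities measured at a single visit "will be evaluated by mixed logistic models, containing the respective variables, with region as a random effect as above". The section does not say which effect measure will be reported from any of these.

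**Power.** The opening of Data analysis states detectable effects as relative risks (20 and 30) for microcephaly alone, from a baseline of 0.025%.

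**The concern.** For PW, the objective and the power statement are on the risk scale and the stated model result is on the odds scale. This is more than detail left for later: the article picks a measure, and that measure does not answer its first objective.

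Three uses of the results depend on this.

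- **Absolute risk.** The Discussion offers the results as risk estimates for allocating resources and as comparison data for later trials without a control arm. An odds ratio cannot serve either purpose alone.
- **Relative risk.** A reader who takes the odds ratio as a relative risk overstates a harmful effect, by more the commoner the endpoint.
- **Variation between regions.** Box 1 also asks what explains differing risk estimates. If baseline risk differs by region, a constant relative risk produces different odds ratios, so part of any apparent effect modification could come from the scale.

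For CH, the objective is risk over two years, and the section names a model without saying what risk estimate will come from it.

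**Working it through.** **1. The plan's own figure.** Inputs from Data analysis: baseline risk p0 = 0.00025, infection probability 10% or 5%, relative risk 20 or 30, α = 0.05 (taken as two-sided, since sidedness is not stated), power 80%. I used the usual two-proportion normal approximation (pooled variance, no continuity correction). The required total is 5880 for relative risk 20 at 10% infected, and 5720 for relative risk 30 at 5% infected. Power is 76.3% and 77.4% at 5000 women, and 80.5% and 81.0% at 6000. The stated range of 5000 to 6000 reproduces. Because it is already on the relative-risk scale, reporting risks would not change it.

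**2. Odds ratio against relative risk.** With p1 = RR × p0,

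OR = [p1/(1 − p1)] / [p0/(1 − p0)], so OR/RR = (1 − p0)/(1 − p1).

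Microcephaly, at the article's own risks (0.025% uninfected, 0.25% to 6% infected):

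| RR | p1 | OR | Excess over RR |
|---|---|---|---|
| 10 | 0.25% | 10.02 | 0.2% |
| 20 | 0.50% | 20.10 | 0.5% |
| 30 | 0.75% | 30.22 | 0.7% |
| 240 | 6% | 255.3 | 6.4% |

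Composite endpoint. No baseline is given, so these baselines are assumptions; true RR = 2:

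| Assumed p0 | p1 | OR | Excess over RR |
|---|---|---|---|
| 1% | 2% | 2.02 | 1% |
| 5% | 10% | 2.11 | 6% |
| 10% | 20% | 2.25 | 12% |
| 20% | 40% | 2.67 | 33% |
| 30% | 60% | 3.50 | 75% |

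Read down the OR column, the second table also shows the regional problem: two regions with the same relative risk of 2 but baselines of 5% and 20% would show odds ratios of 2.11 and 2.67.

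**3. Odds ratio against absolute risk.** Fix OR = 2 and solve p1 = o/(1 + o) with o = 2 × p0/(1 − p0):

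| p0 | p1 | Risk difference (points) | RR |
|---|---|---|---|
| 0.025% | 0.05% | 0.025 | 2.00 |
| 10% | 18.2% | 8.2 | 1.82 |
| 30% | 46.2% | 16.2 | 1.54 |

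The same odds ratio fits risk differences from 0.025 to 16.2 points, so on its own it fixes no absolute risk. The mixed-model odds ratio is also conditional on the region effect, a further step from a population risk ratio. That step cannot be sized, because no between-region variance is given.

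**4. CH.** A Cox model with its baseline cumulative hazard H0 gives a 24-month risk of 1 − exp[−H0(24) × exp(linear predictor)]. The named model can therefore deliver the objective; the section just does not say that it will. Development is assessed at visits at 1–3, 4–6, 12 and 24 months (CH study design), so a detected abnormality is known only to have arisen between visits, and many event times will be tied.

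**The case against.** The strongest case against has four parts.

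- **The analysis plan is not shown.** The PW section defers to a pre-specified plan, and the sentence on odds ratios describes one model's output without excluding others. The two-by-two table behind the chi-square test contains the crude risks. This stands in part: one cannot say that risks will never be reported. But the descriptive analysis promised in that section concerns the women's characteristics, crude risks are unadjusted, and the one effect measure stated for the endpoint differs from the objective.
- **The model is not wrong.** Standardised risks can be computed from the planned mixed model. This stands. The issue is which estimates are reported, not which model is fitted.
- **The endpoint may be rare.** The article gives risks only for microcephaly, where the odds ratio is a close stand-in for the relative risk. A reader might infer that the composite is known to be common and the overstatement therefore large. The article does not support that: it gives no composite baseline and ties the endpoint to a definition still in development. The honest range runs from negligible to material. Rarity would in any case not supply the absolute risk.
- **The analysis is called exploratory, and tests and sample size are unaffected.** This stands, and it limits the severity.

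For CH, a reader might infer that a hazard ratio is the stated output and that no absolute risk can be produced. Neither is supported. The section never names a hazard ratio, survival techniques include cumulative incidence, and a Cox model can yield 24-month risks. If a hazard ratio were reported and read as a relative risk, assumed 24-month risks of 20% and 40% would show as ln(0.6)/ln(0.8) = 2.29 instead of 2, but that is conditional on a reporting choice the article does not make.

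**Conclusion.** The point holds for PW as an explicit mismatch between the first primary objective and the stated model result. The missing absolute risk follows whatever the baseline. The gap between odds ratio and relative risk depends on it: 0.2% to 6.4% for microcephaly at the article's own figures, and, for a relative risk of 2, from 1% at an assumed composite baseline of 1% to 75% at 30%. The composite figures rest wholly on assumed baselines.

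For CH the point is smaller: no absolute- or relative-risk estimate is named, although the objective asks for both.

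This should be fixed, but it does not invalidate the planned tests, the models or the sample size.

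**What to change.** **PW.** State that the main estimates are the standardised risks in infected and uninfected women, their difference and their ratio, with 95% confidence intervals that allow for region. Obtain them from the fitted mixed model, by averaging predicted risks over the cohort with infection status set each way and over the region effect, or from a log-link or modified-Poisson model. Keep the odds ratio as a secondary result, labelled as conditional on region. Report the crude risks by group beside these.

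**CH.** State that the main estimates are the 24-month cumulative risk by exposure group, with risk difference and risk ratio and 95% confidence intervals. Preferably take them from a model that respects detection at scheduled visits, such as a discrete-time model on the visit intervals. If the Cox model is kept, derive the 24-month risks from it.

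**Cost.** A few lines in the analysis plan and some post-estimation code. No new data and no change to the sample size.
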